## Abstract

**Background:**

Endovascular aortic repair is considered the standard procedure in treating patients diagnosed with pathologies of the abdominal aorta with suitable anatomy. Open surgery remains an option mostly for patients not suitable for endovascular surgery. Colonic ischemia is an important and life-threatening postoperative complication of these procedures.

**Objective:**

The aim of this study is to evaluate the clinical value and safety of performing a planned sigmoidoscopy and biopsy for detection of colonic ischemia in patients undergoing elective aortic surgery. We also aim to develop prediction scores which could identify patients at risk for colonic ischemia and facilitate their timely treatment.

**Methods:**

The trial is designed as a prospective study. The decision for aortic surgery and eligibility for these procedures will be ascertained according to current guidelines. Afterward, screening of the patient for the remaining inclusion and exclusion criteria will occur. If eligibility for study inclusion is confirmed, the patient will be informed about the aims of the study and all study-specific procedures (sigmoidoscopy and biopsy) and asked to provide informed consent.

**Results:**

The primary end point is the proportion of patients diagnosed endoscopically with subclinical and clinically relevant colonic ischemia among all patients undergoing aortic surgery. Patient recruitment started on June 2021. The final patient is expected to be treated by the end of June 2023. Institutional Review Board review has been completed at the University of Halle (Saale; reference #052-2021).

**Conclusions:**

this shows that sigmoidoscopy can be performed safely and is effective for the timely diagnosis of colonic ischemia in these patients, this could result in its routine implementation in both elective and emergency settings.

**Trial Registration:**

German Clinical Trials Register DRKS00025587; https://www.drks.de/drks_web/navigate.do?navigationId =trial.HTML&TRIAL_ID=DRKS00025587

**International Registered Report Identifier (IRRID):**

DERR1-10.2196/39071

## Introduction

Endovascular aortic repair (EVAR) is considered the standard procedure in treating patients diagnosed with abdominal aortic pathologies and suitable anatomy. Open surgery remains an option mostly for patients not suitable for endovascular surgery. Colonic ischemia is known as a severe complication after both open and endovascular aortic surgery. Its incidence is well described, and even with modern treatment options, colonic ischemia carries a high mortality rate. One of the assumed causes of colonic ischemia after aortic surgery is reduced blood flow via the inferior mesenteric artery. The origin of the vessel is either ligated during open repair (OR) or excluded from antegrade perfusion during EVAR. Reimplantation is rarely performed during OR and not possible during EVAR. Moreover, stenosis or occlusion of the inner iliac arteries may contribute to ischemia of the distal colon and rectum.

When compared to OR, EVAR is associated with reduced invasiveness, less general anesthesia, shorter operation times, less blood loss, and lower postoperative pain. Two meta-analyses showed lower short-term mortality in patients undergoing EVAR when compared to OR [1,2]. Nevertheless, there are no advantages in terms of long-term mortality [3]. In the emergency setting, no advantages for EVAR in terms of short- or long-term outcomes could be found [4-7]. Because of the evidence and experience from the last 30 years, most vascular surgeons now consider EVAR as the treatment of choice in the elective and emergency context, leaving OR for individual cases with anatomic unsuitability for EVAR, mycotic abdominal aortic aneurysms, conversion after early or delayed failure or infection of EVAR, or patient preferences (Figure 1).

**Figure 1 figure1:**
[figure not shown]
Flowchart of surgical procedures. AAA: adominal aortic aneurysm; bEVAR: branched endovascular aortic repair; fEVAR: fenestrated endovascular aortic repair; OR: open repair.

As already stated, the risk of developing colonic ischemia is present in both endovascular on open treatment of aortic aneurysms. In a meta-analysis involving 13 studies reporting outcomes of colonic ischemia after elective aortic repair comprising 162,750 patients (78,151 EVAR and 84,599 OR), all studies found a higher risk of colonic ischemia for OR than for EVAR (2.1%-3.6% vs 0.5%-1%; combined odds ratio 2.7, 95% CI 2.0-3.5) [8].

Other studies highlight the low incidence but high fatality of colonic ischemia. Lowe et al [9] reported in a systematic review and meta-analysis including 5 cohort studies and 3 case reports with 6184 infrarenal elective EVARs an, incidence of colonic ischemia of 0.5% to 2.8%. In these patients, fatality ranged from 35% to 80%. The authors highlight the importance of identifying risk factors and establishing prophylactic measures in patients with an increased risk of developing these severe complications after infrarenal EVAR. In a database analysis from the United States on 89,967 patients who underwent aortic surgery, the overall incidence of colonic ischemia was 2.2%. The patients who developed colonic ischemia were at increased risk for mortality (37.8% vs 6.7%) [10]. Studies reporting on the use of colonoscopy for identifying patients at risk for colonic ischemia have been published, mostly regarding patients in an emergency context. In both patient collectives—elective and emergent—high mortality rates have been reported. In a study by Champagne et al [11] that included 88 patients who underwent emergent aortic reconstruction because of ruptured aortic aneurysm, colonoscopy was performed in 62 patients who survived for more than 24 hours. Bowel ischemia was documented in 35% of patients. Of these, 16 patients had grade I or grade II ischemia and repeat endoscopy. Grade I ischemia was defined as mucosal ischemia; grade II ischemia was characterized by involvement of the mucosa and the muscularis layers; and grade III ischemia was described by transmural ischemia, gangrene, and perforations. Nine patients needed bowel resection because of grade III ischemia; two procedures were performed because of worsening ischemia discovered at repeat colonoscopy. In another meta-analysis, the accuracy of routine endoscopy in diagnosing colonic ischemia after abdominal aortic aneurysm repair was analyzed. In all, 718 patients were included (44% underwent elective, 56% emergent, and 6% endovascular repair). Among all patients, 20.8% were identified with colonic ischemia (6.5% grade III). The pooled diagnostic odds ratio for all grades of colonic ischemia on endoscopy was 26.6 (95% CI 8.86-79.88) [12]. In a study from Germany, the incidence of colonic ischemia among patients who underwent aortic surgery was 2.4%. Colonic ischemia was predominantly diagnosed by endoscopy (74%). In-hospital mortality was increased in the colonic ischemia group (26.7% vs 2.9%; *P*<.001) [13].

The aim of this study is to evaluate the clinical value and safety of performing a planned sigmoidoscopy and biopsy for detection of colonic ischemia in patients undergoing elective aortic surgery. We also aim to develop prediction scores which could identify patients at risk for colonic ischemia and facilitate their timely treatment. If this study shows that sigmoidoscopy can be performed safely and is effective for diagnosing colonic ischemia in these patients, this could result in its routine implementation in both elective and emergency settings.

## Methods

### Study Design

The trial is designed as a prospective study. The decision for aortic surgery and eligibility for these procedures will be ascertained according to the current guidelines from the German and European societies (Deutsche Gesellschaft für Gefäßchirurgie [DGG; German Society of Vascular Surgery and Vascular Medicine], Society of Vascular Surgery [SVS], and European Society of Vascular Surgery [ESVS]) [14-16]. Afterward, screening of the patient for the remaining inclusion and exclusion criteria will occur. If eligibility for study inclusion is confirmed, the patient will be informed about the aims of the study and all study-specific procedures and asked to provide informed consent. This will take place prior to the planned aortic surgery.

### End Points

The primary end point is the proportion of patients diagnosed endoscopically with subclinical and clinically relevant colonic ischemia among all patients undergoing aortic surgery.

The secondary end points are the proportion of patients requiring surgery for colonic ischemia after aortic surgery, the proportion of patients requiring stoma formation for colonic ischemia, perioperative in-hospital morbidity and mortality measured according to the Clavien-Dindo classification of surgical complications, length of hospital stay, and frequency of reoperation.

### Study Population

The inclusion criteria are the following: elective open or endovascular surgery for abdominal aortic aneurysm (Figure 1), provision of written informed consent prior to any study-specific procedures and willingness to comply with treatment and follow-up, and age ≥18 years.

The exclusion criterion is any serious and/or unstable pre-existing medical, psychiatric, or other condition that could interfere with the patient’s safety, provision of informed consent, or compliance with study procedures.

### Number of Trial Participants

We assume that the rate of colonic ischemia diagnosed by sigmoidoscopy within 48 hours after the operation would be 10% in asymptomatic patients. In the current literature, the incidence of colonic ischemia diagnosed by clinical suspicion only in symptomatic patients is approximately 5%. This rate plus 10% of the 95% of asymptomatic patients results in an overall rate of patients with signs of colonic ischemia of 14.5%. In turn, this results in a 1-armed binomial distribution with 120 cases to be compared to the incidence reported in the literature (5%; α=5%; 1-β [power]=80%) [17].

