#### Sigmoidoscopy

At the time of sigmoidoscopy, the following information will be assessed and documented in a protocol: date of sigmoidoscopy; examination time; sigmoidoscopy findings (grade I: mucosal ischemia; grade II: mucosa and the muscularis layers; grade III: transmural ischemia, gangrene, and perforations; if grade III ischemia is detected, no biopsy will be performed); complications of the sigmoidoscopy; blood results, including C-reactive protein, lactate, leukocytes, glomerular filtration rate, creatinine, and hemoglobin; and a checklist to assess the degree of clinical suspicion of colonic ischemia filled out by the surgeon (if the checklist does not indicate a suspicion of colonic ischemia this will be defined as subclinical).

At the time of biopsy result, the following information will be assessed and documented in a protocol: date of result, biopsy findings differentiating ischemia in nongangrenous type (mucosal atrophy, edema, hyperemia, mild acute inflammation), and gangrenous type (acute wall necrosis), and ischemia grade.

Independent observers, blinded to the macroscopical findings of the sigmoidoscopy and the clinical course of the patient, will assess the results of the biopsy.

The tissue will be preserved for immunohistochemistry and RNA analysis of ischemia markers (eg, fatty acid binding protein).

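### Comparing the rate found by scoping every patient with a 5% literature rate found on clinical suspicion does not measure what planned sigmoidoscopy adds; the checklist-negative yield does

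*Protocol article*

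**What the plan says.** All references are to the protocol article.

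- **End Points.** The main outcome is defined as "the proportion of patients diagnosed endoscopically with subclinical and clinically relevant colonic ischemia among all patients undergoing aortic surgery". It pools cases that were clinically suspected with cases that were not.
- **Number of Trial Participants.** The benchmark is described thus: "the incidence of colonic ischemia diagnosed by clinical suspicion only in symptomatic patients is approximately 5"%. The yield of scoping is an assumption: "We assume that the rate of colonic ischemia diagnosed by sigmoidoscopy within 48 hours after the operation would be 10% in asymptomatic patients". The two are then added: "This rate plus 10% of the 95% of asymptomatic patients results in an overall rate of patients with signs of colonic ischemia of 14.5"%. The design follows: "this results in a 1-armed binomial distribution with 120 cases to be compared to the incidence reported in the literature", with the parameters "5%; α=5%; 1-β [power]=80"%. Whether α is one-sided or two-sided is not stated.
- **Analysis of End Points.** The primary end point is reported as one proportion with a 95% CI. No test is named, and no separate analysis of the subclinical part is described.
- **Evaluation and Follow-up, Sigmoidoscopy.** The surgeon fills out a checklist of clinical suspicion, and "if the checklist does not indicate a suspicion of colonic ischemia this will be defined as subclinical". It is recorded at the time of sigmoidoscopy. Blinding to the macroscopic findings is specified only for the biopsy readers.
- **Objective and Introduction.** The aim is the clinical value and safety of a planned sigmoidoscopy with biopsy after elective aortic surgery.

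**The concern.** The two rates being compared count different things. The trial's rate counts every case of ischemia, of any grade, seen when all patients are scoped. The 5% counts cases that came to light because someone suspected them, in other cohorts. The expected 14.5% is that 5% plus 9.5 points of cases that only scoping would find, and those 9.5 points are the study question.

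The comparison with 5% therefore moves with two quantities: the yield in unsuspected patients, and the local clinical rate. If the centre's clinical rate is below 5%, a useful yield can be hidden. If it is above 5%, part of the excess has nothing to do with planned scoping. A reader who takes the 5% as the yardstick could draw the wrong conclusion about routine sigmoidoscopy in either direction.

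**Working it through.** **Inputs from the article.** Benchmark p0 = 5%; assumed yield in asymptomatic patients y = 10%; N = 120; α = 5%. Cited incidences: 0.5% to 1% for elective endovascular repair and 2.1% to 3.6% for elective open repair; 0.5% to 2.8% for elective infrarenal endovascular repair; 2.2% in a US database; 2.4% in a German study.

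**Assumptions made here.** Every patient is scoped. Every clinically apparent case is also seen at endoscopy. The 2.4% stands in for a suspicion-led clinical rate. A clinical rate of 1% and a yield of 5% are illustrative.

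**Step 1, the plan's own figures.** Expected rate = 0.05 + 0.10 × 0.95 = 0.145, which agrees with the article. The 120 does not reproduce as a one-arm size for 5% against 14.5% at 80% power: standard approximate and exact methods give between 48 and 108. At N = 120 the one-arm power is 94% to 97% (Step 3, last line), so the trial is not too small for the stated comparison. That is a separate matter and is not pursued here.

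**Step 2, the rule implied by the comparison.** X ~ Binomial(120, p), and the rule is the smallest r with P(X ≥ r | p = 0.05) ≤ α.
- One-sided 5%: r = 11, since P(X ≥ 11) = 0.038.
- Two-sided 5% (2.5% in the upper tail): r = 12, since P(X ≥ 12) = 0.017.

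The two-sided rule is also what results from reading an exact 95% CI against 5%: for 11/120 the lower limit is 4.7%, for 12/120 it is 5.3%.

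**Step 3, yield fixed and clinical rate varied.** Total rate p = c + y(1 − c), where c is the local clinical rate and y = 10%.

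| c | p | P(X ≥ 12) | P(X ≥ 11) |
|---|---|---|---|
| 1% (assumed) | 0.01 + 0.10 × 0.99 = 10.9% | 67% | 77% |
| 2.4% (German study) | 0.024 + 0.10 × 0.976 = 12.2% | 80% | 88% |
| 5% (benchmark) | 0.05 + 0.10 × 0.95 = 14.5% | 94% | 97% |

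What scoping finds in unsuspected patients is the same in every row, yet the chance of exceeding 5% changes by 27 points (two-sided) or 20 points (one-sided).

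**Step 4, a useful yield that the comparison would mostly miss.** With c = 2.4% and y = 5% (assumed), p = 0.024 + 0.05 × 0.976 = 7.3%. Detection rises by a factor of 7.28/2.4 = 3.0. The chance of exceeding 5% is 16% (≥ 12) or 26% (≥ 11).

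**Step 5, the direct estimate from the trial's own data.** On the protocol's assumptions, 120 × 0.95 = 114 patients are checklist-negative, and 10% of 114 = 11.4, about 11 cases. 11/114 = 9.6%, exact (Clopper-Pearson) 95% CI 4.9% to 16.6%. No external rate enters.

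**The case against.** **No test is planned.** A reader might infer that the trial will be declared a success or failure against 5%. The documents do not support that: the analysis section plans a proportion with a confidence interval, and the comparison appears only in the sample-size section. This stands, and it limits the point to the sizing rationale and to interpretation. But 5% is the only yardstick the article gives, and the interval invites being read against it.

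**Success with no added yield.** A reader might also infer that 5% would readily be exceeded even if scoping found nothing new. That needs local clinical rates well above anything cited. With zero yield, the chance of 12 or more cases is 1.7% at a clinical rate of 5%, 0.1% at 3.6% (the highest elective rate cited) and under 0.01% at 2.4%. On the article's figures, the realistic risk is the opposite one, in Steps 3 and 4.

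**The split may be planned elsewhere.** The end point names both components, and the checklist defines the subclinical one. It would be wrong to say that the checklist goes unused; a full protocol or SAP may tabulate it. What the article does fix is the pooled rate as primary and the 5% as its comparator, and that pairing is poorly matched to the aim.

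**The result is already known.** The Introduction cites a meta-analysis of routine endoscopy: "Among all patients, 20.8% were identified with colonic ischemia (6.5% grade III"). It would be tempting to say that exceeding 5% therefore teaches nothing. Those patients were 56% emergent and only 6% had endovascular repair, whereas this trial is elective and treats endovascular repair as standard. The figure cannot carry that argument.

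**The checklist has limits of its own.** It is recorded at the time of sigmoidoscopy, and the surgeon is not said to be unaware of the findings. Some patients unsuspected at 24 to 48 hours may develop symptoms later. Both objections stand and are built into the fix.

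**Conclusion.** The concern holds in a limited form. Comparing the pooled endoscopic rate with a literature rate found on suspicion does not measure what planned sigmoidoscopy adds, because the answer depends on the local clinical rate as well as on the yield. With the protocol's 10% yield, the chance of exceeding 5% runs from 67% to 94% (two-sided) or 77% to 97% (one-sided) as the clinical rate goes from 1% to 5%. With a 5% yield at the cited 2.4%, it is 16% or 26%.

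These figures rest on complete scoping of 120 patients and on the assumptions listed; the 1% rate and the 5% yield are illustrative. The article reports that 74% of the ischemia in the German study was diagnosed by endoscopy, and using its 2.4% as a suspicion-led rate is our reading. The point is worth correcting, but it does not invalidate the trial: the pooled proportion remains a sound description, and the data for the better estimate are already collected.

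**What to change.** 1. Keep the pooled primary end point as a descriptive proportion with its 95% CI. State that the literature 5% is context and that an excess over it will not be read as added yield.
2. Name as the key estimate the proportion of checklist-negative patients with endoscopic ischemia, with an exact 95% CI, and show it by grade I, II and III.
3. Require the surgeon to complete the checklist before the endoscopic findings are known, and record that order.
4. State that this is added detection at 24 to 48 hours. It is not evidence that earlier detection improves outcome, which a study without a control group cannot show.

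**Cost.** No extra patients and no new examination; at most a record of when the checklist was completed. The headline figure becomes smaller, about 10% against 14.5%. If suspicion is raised in more than 5% of patients, the denominator falls below 114 and the interval widens. Recruitment began in June 2021, so the change may need an amendment submitted to the ethics committee. For patients already enrolled, the order of checklist and endoscopy would have to be established from records or declared unknown.

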### Analysis of End Points

Analysis of the primary end point will occur as soon as all patients have undergone aortic surgery and sigmoidoscopy and are discharged from the hospital. The primary end point will be presented as a proportion with a 95% CI.

Secondary end points (proportion of patients proceeding to surgery for colonic ischemia after aortic surgery, perioperative in-hospital morbidity, and mortality measured according to the Clavien-Dindo classification of surgical complications) will also be analyzed once the patient has been discharged from the hospital after the respective procedure. The incidence of complications will be presented as a proportion with a 95% CI stratified by the highest Clavien-Dindo grade of all complications that occurred in each patient.

### Recruitment

Participants will be recruited at the institution carrying out the study. Dedicated screening for trial participation will be performed when open and endovascular aortic surgery for the patient is discussed by the interdisciplinary vascular board. If the patient is selected to undergo open or endovascular surgery, informed consent will be presented to the patient by a physician within 24 hours before surgery.

### Trial Implementation and Enrollment

#### Trial Procedures

All relevant trial procedures are displayed in Table 1. The computed tomography (CT) scan is not a study-specific procedure, as every patient who undergoes open or endovascular aortic surgery will receive a preoperative CT scan as routine care.

**Table 1 table1:** Time and events table.

Required measures	Screening/trial entry	Aortic repair	Sigmoidoscopy 24-48 h after aortic repair
Verification of inclusion and exclusion criteria	✓		
Informed consent	✓		
Computed tomography	✓		
Ascertainment of data as detailed in Evaluation and Follow-up	✓	✓	✓
Ascertainment of primary end point			✓
Follow-up exams at the discretion of the treating physician			
Surgery		✓	

#### Sigmoidoscopy

A standard sigmoidoscopy (from the rectum to the transition of the sigmoid to the descending colon) will be performed. The macroscopically visible ischemia will be graded according to the following scheme: grade I = mucosal ischemia; grade II = involvement of the mucosa and the muscularis layers; and grade III = transmural ischemia, gangrene, and perforations.

A biopsy should be always performed, when possible, in macroscopically suspicious areas. When no macroscopic suspicion is present, a biopsy should be taken in the sigmoid colon. Biopsy should differentiate between normal mucosa, the nongangrenous type of ischemia (mucosal atrophy, edema, hyperemia, mild acute inflammation), and the gangrenous type of ischemia (acute wall necrosis).

### Evaluation and Follow-up

#### Trial Entry

Upon trial entry, the following information will be assessed: date of birth and sex; date of diagnosis; diagnosis; symptoms or clinical history of chronic mesenteric ischemia; in case of aneurysm, the maximal transversal diameter; the length of aneurysm neck; history of cardiovascular diseases; CT findings (patency of abdominal branches: superior mesenteric artery, inferior mesenteric artery and celiac artery, lumbar arteries, hypogastric arteries); Eastern Cooperative Oncology Group (ECOG) performance status; and American Society of Anesthesiologists (ASA) status.

